**FIGURE 2 F2:**
[figure not shown]
A cross-over design of the clinical trial with probiotics. T1 denotes the time of first visit when participants were assessed with the PROCOG cognitive battery. The two groups received both probiotic and placebo tablets but in a reverse order. At T2 the participants brought back baseline urine and stool samples and their blood was collected. They also got the first set of probiotic/placebo tablets. All examinations and procedures from T1 and T2 were repeated at T3 when the participants got the second set of probiotic/placebo tablets. All examinations and procedures similar to T3 were repeated at T4 and T5.

All 91 participants were divided into two subgroups based on the order in which they completed the electronic registration form. One subgroup included participants with odd position numbers; the other one had even numbers. After checking for statistically significant sociodemographic differences between two subgroups, a few individuals were exchanged between these subgroups. This ensured that both subgroups matched in age, education, gender, and ALBAV scores before the start of the trial. Unexpectedly, 19 participants did not wish to come for testing in person due to the COVID-19 pandemic. Therefore, they were transferred from in-person to online assessment. These individuals were removed from the original allocation to online subgroups of participants.

A crossover design did not strictly confine one group of individuals to an intervention or placebo. Each group received both placebo and probiotics in tandem for 3 months each, but in reverse order. Members of group A start with a 3-month use of probiotics and continue with a 3-month use of placebo. The order of tablets is reversed for group B. There was no washout period between treatments.

Both participants and administrators were blinded to the type and order of intervention and placebo.

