Each participant was evaluated during four visits at the University Hospital Kralovske Vinohrady, Prague, or the National Institute of Mental Health, Klecany, Czech Republic. A subset of the participants agreed with the last follow-up visit (*n* = 16 in group A, *n* = 18 in group B). They continued the study for a further 3 months without any intervention after the study termination to see the long-term effect of microbiome changes. Therefore, they had the fifth visit in addition. The first, third, fourth, and fifth visits were planned at 3-month intervals with a tolerance of ±1 week. The second visit was added 1 week after the first one to let participants take test tubes and bring back baseline stool and urine samples.

All measures were included at each visit except the first two. For logistical reasons, all procedures were divided into two visits at the beginning of the trial. Participants were administered a cognitive battery, completed self-report measures, and received test tubes to collect stool and urine samples during the first visit. The second visit included a physical fitness evaluation and sample collection. Participants also received either probiotic or placebo tablets and fiber or placebo fiber tablets for the next 3 months. A detailed description of each visit is described in Supplementary material 1.

Whenever possible, the administration of cognitive tests was conducted by the same administrator for individual participants throughout the whole period of the study until the fourth visit. Only two administrators performed cognitive testing on the fifth visit to each institution.

The participants received 3,000 Czech crowns for their participation at the end of the study (i.e., the fourth visit), which is equal to 123 EUR or 140 USD at the current currency exchange.

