#### Sample preparation

##### Serum sample collection and preparation

A nurse at each center took 13 ml of blood samples from participants who came for blood collection between seven and nine in the morning and who consumed their last meal the evening before. Blood was collected into two kinds of evacuated blood vacuum tubes (Vacuette 9 ml Serum and Vacuette 9 ml K3EDTA)—one for plasma and the second one for serum. After collection, the blood was immediately centrifuged at 4,000 rpm for 10 min, and the whole supernatant was transferred into a 5 ml Eppendorf tube, vortexed for 30 s, and divided into cryotubes for storage at -84^°^C till the analysis.

Before metabolomic High-Performance Liquid Chromatography Mass Spectrometry (HPLC-MS) analysis, one aliquot of serum (300 μl) thawed on ice, 600 μl of acetonitrile was added and vortexed for 30 s, and kept on ice for 10 min. Then, all samples were centrifuged at 13,500 rpm for 10 min at 4°C, and the liquid phase was transferred to vials for proper liquid chromatography-mass spectrometry (LC-MS) analysis.

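### Within-group cognitive change from T1 to T3, T4 or T5 in the in-person participants is potentially confounded with visit format; the A-versus-B comparison is not

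*Protocol article*

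**What the plan says.** The Trial design section of the protocol article describes a split baseline: "All measures were included at each visit except the first two", and "For logistical reasons, all procedures were divided into two visits at the beginning of the trial". For the first visit (T1) it says: "Participants were administered a cognitive battery, completed self-report measures, and received test tubes to collect stool and urine samples during the first visit". For the second (T2), one week later: "The second visit included a physical fitness evaluation and sample collection". The Figure 2 legend then says "All examinations and procedures from T1 and T2 were repeated at T3", and "All examinations and procedures similar to T3 were repeated at T4 and T5".

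The section on serum collection describes participants "who came for blood collection between seven and nine in the morning and who consumed their last meal the evening before". The article refers further visit detail to Supplementary material 1, which is not at hand.

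Proposed analysis names two tests: an unpaired t-test between groups at each time point, and a paired t-test within subjects between time points. The Figure 4 legend sets hypotheses for both kinds of comparison. Within groups it expects improvement after probiotics and no favourable change after placebo. Cognition is a primary outcome. It was tested in person in 72 participants; the other 19 were tested online and are outside this point.

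**The concern.** A paired test from T1 to T3 has no concurrent control. It attributes to treatment whatever else changed between the two occasions. One thing that changed by design is the visit itself: T1 had no blood draw and no fitness tests, and T3 had both on the same occasion as a cognitive battery of about an hour.

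The change also falls unevenly across the crossover. Group A's probiotic interval (T1 to T3) spans it. Group B's probiotic interval (T3 to T4) does not.

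At stake is the reading of the first-period within-group hypotheses. Figure 4 itself is not shown, but from its legend and the treatment order these appear to be H1a (group A, probiotic) and H1b (group B, placebo). If the T3 format depressed scores, a real gain in A could be hidden and B could appear to decline on placebo. If it raised them, the reverse would follow.

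**Working it through.** **1. Visit content, side by side (in-person participants)**

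| Visit | Cognition | Blood draw and fitness tests |
|---|---|---|
| T1 | yes | no |
| T2 (one week later) | no | yes |
| T3, T4, T5 | yes | yes, same visit |

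The cognitive contrasts that cross the format change are T1 to T3, T1 to T4 and T1 to T5. T3 to T4 does not cross it. A versus B at any one visit does not cross it either, because the schedule is the same in both groups.

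**2. The plan's own figures**

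The Power calculation section gives detectable effects at 80% power and two-sided α = 0.05. Group sizes are not in the text, so they were inferred by solving the exact noncentral-t power for d.

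| Test | Stated d | Recomputed d |
|---|---|---|
| Paired, all participants | 0.43 | 0.432 (n = 44), 0.427 (n = 45) |
| Paired, in-person only | 0.51 | 0.511 (n = 32) |
| Two-sample, all participants | 0.59 | 0.594 (45/46) |
| Two-sample, in-person only | 0.67 | 0.670 (36/36), 0.674 (32/40) |

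All four reproduce. None depends on the visit schedule, so this point changes no stated figure.

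**3. What a format shift would do to the within-group test**

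The documents give no size for such a shift, so c is an assumption, in units of the SD of the change score. With no true treatment effect, the paired test has noncentrality c·√n. At n = 32, against a nominal 5%, the two-sided rejection rate is:

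- c = 0.1: 8.5%
- c = 0.2: 19.5%
- c = 0.3: 37.6%

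**4. The same idea on the score scale**

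Assume a retest correlation r = 0.7 and a combined visit that lowers scores by 0.1 or 0.2 SD of the score. Both are assumptions.

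- SD of change = √(2(1 − 0.7)) = √0.6 = 0.775 SD of the score.
- Shift in change units: 0.1/0.775 = 0.129 and 0.2/0.775 = 0.258.
- Group A at the stated d = 0.51, n = 32: the effective d is 0.51 − 0.129 = 0.381 or 0.51 − 0.258 = 0.252. Power falls from 80% to 55% or 28%.
- Placebo group with no true change: a significant decline occurs with probability 10.5% or 29.3% (n = 32), and 12.2% or 35.7% (n = 72 − 32 = 40). The nominal rate in that direction is 2.5%.

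A shift upward would mirror these figures.

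**5. What it does to the comparison between groups**

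The same shift was added to the change scores of both groups (20,000 simulated trials, groups of 33 and 39). The mean bias was about 0. The rejection rate was 5.0%, 5.2% and 4.8% at c = 0, 0.3 and 0.5. The shift cancels.

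**The case against.** The tempting stronger reading is that T1-to-T3 change is in fact biased, probably downward, by hunger and fatigue at T3. The documents do not support it, for these reasons:

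- The article does not give the order of procedures within T3, whether participants ate before testing, or the time of day and fasting state at T1. If the battery came first, or after a meal, the draw and fitness tests may have mattered little. Supplementary material 1 may settle this.
- The physical load is light: 30 seconds of lifting a 1 kg dumbbell, a walk of 2 × 17 m and 30 seconds of chair stands. The blood sample is 13 ml. The long battery and the questionnaires were already part of T1.
- Table 1 and its text say that the tests were given in the same order by the same rater, so the cognitive session itself was meant to be standardised.
- The direction is open. The Clock Drawing Test and the Trail Making Test reuse one form, and practice would tend to raise T3 scores.

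A reader might also infer that the trial's treatment comparison is compromised, or that the article wrongly treats the two probiotic intervals as replicates. Neither follows. The between-group test is planned and unaffected, and the article nowhere calls the intervals replicates.

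It is also fair to say that an uncontrolled paired test is exposed to any time or practice effect, whatever the visit layout, and that the split is disclosed and explained as logistical.

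All of this stands against a claim of demonstrated bias. It does not remove the narrower point: the format did change between T1 and T3, one of the two named tests runs across that change, and neither a constant test order nor a constant rater equalises what else the visit contained.

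**Conclusion.** The point holds in a limited form. For in-person participants, the within-group paired tests of cognition from T1 to T3, T4 or T5 are potentially confounded with visit format, alongside any other time or practice effect. The schedule that creates this is stated in the article. The size and direction of its effect are not known.

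The error rates and power figures above rest on an assumed shift, in part on an assumed retest correlation of 0.7, and on group sizes inferred from the stated detectable effects. They illustrate sensitivity and are not estimates. The A-versus-B comparison is free of the problem, and so, for this particular difference, is T3-to-T4 change. Severity is minor to moderate.

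**What to change.** The study ran to May 2022, so the visits cannot be rearranged. The change is to the analysis:

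1. Do not read within-group cognitive change from T1 to T3, T4 or T5 as a treatment effect. Report it descriptively, with a sentence on the difference in visit format.
2. Base the T3 cognitive inference on A versus B adjusted for the T1 score, by ANCOVA or by the difference between groups in change from T1. This replaces both the unadjusted unpaired t-test and the within-group paired t-test for that question.
3. State in the report the order of procedures at T3 and, if recorded, the time of day and fasting state at T1 and T3, so that readers can judge what risk remains.

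**Cost.** A few sentences and no new data. H1a and H1b become descriptive. Under the assumed r = 0.7, the paired in-person test detects 0.51 × √0.6 = 0.40 SD of the score. The adjusted between-group test detects about 0.67 × √(1 − 0.7²) = 0.48 SD, against 0.67 SD for the unadjusted test now planned. The controlled comparison is therefore somewhat less sensitive than the paired test it replaces, and more sensitive than the unpaired one.

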### Probiotics and placebo

Participants were offered to take one probiotic/placebo tablet each day along with two fiber/placebo fiber tablets. The time of tablet consumption was up to the participant. More details about the content of the probiotic and placebo tablets are available in Supplementary material 2. All the tablets were provided by the company NEXARS (Brno, Czech Republic).

Participants were asked about the adverse side effects of the intervention at the end of each 3 months using a structured list of hypothetical side effects.

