## Anticipated results and hypotheses

Our hypotheses are visualized in Figure 4. We expected a logical and favorable change in the cognitive tests, psychological measures, surrogate biological markers, and other measures following the 3-month probiotic treatment. Participants with at least one apoE four alleles would have worse results and, therefore, may benefit from probiotics more.

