## Discussion

We prepared the first 6-month clinical trial to explore the effect of human probiotics in individuals with possible memory deficits. The aim was to include younger elderly individuals between 55 and 80 years of age for several reasons. This population is more prevalent and has a higher frequency of memory impairment than younger people. In addition, they are at the right age for memory improvement and interventions before they get too old or develop dementia.

We believe that the best target population includes individuals who are neither cognitively healthy nor suffering from dementia. On the one hand, healthy cognitive status is not necessary to improve. It may result in ceiling results without being able to observe a change after any intervention. On the other hand, patients with dementia have an advanced pathological processes in their brains. Managing their cooperation in complex studies of this kind is likely logistically costly or virtually impossible (e.g., taking stool samples in a standard manner to special test tubes within a certain time), and their comorbidities might affect the resulting data. Thus, individuals with mild memory deficits are ideal candidates for studies of probiotic effects. They need to improve their memory, and a positive change in test scores and other measures could be seen. However, it is problematic to find such individuals, motivate them to cooperate long-term, and achieve sufficient participant numbers after the exclusion of those with confounding factors (brain, psychiatric, and gastrointestinal diseases, among other conditions). This is highlighted by the fact that 724 individuals interested in our probiotic study using the electronic questionnaires were reduced to 91 (13%) eligible participants only, i.e., a ratio of eight interested persons to one included person in the study.

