We chose an intervention using probiotics and prebiotics. A relationship between the gut microbiota and brain functions is considered in several diseases or conditions (Marotta et al., 2019; Salami, 2021; Handajani et al., 2022; Klann et al., 2022; Mukilan, 2022; Xiang et al., 2022). If proven effective, this natural way would be an easily feasible approach to prevent or postpone more pronounced memory decline or improve mood or anxiety in the elderly. In our comprehensive study, we decided to explore different aspects of brain functioning, physical performance, and blood, urine, and stool changes in response to probiotics with prebiotics. We use an explorative approach to determine which measures are influenced due to the intervention. We chose a crossover study design to ensure active intervention for each participant, which may achieve higher compliance and allow us to use each participant as a control for their own scores.

Probiotic treatment was intended for 3 months. A longer interval would prolong the duration of the study, make the trial more logistically complicated, and decrease participants’ compliance with the study. Three months of treatment was used in another related study (Handajani et al., 2022). The duration of our grant support also limits us. Our study was extended to 9 months for additional examinations to see the long-term effect of the intervention in a subset of participants.

The number of assessments and two types of tablets with a change after 3 months required careful management and sufficient and different personal resources and skills, facility equipment, and expert experience in many disciplines. We balanced recruitment with examinations and space capacities. This was the reason for establishing two centers for performing the study and limiting the number of participants included. Unfortunately, the COVID-19 pandemic complicated such a comprehensive clinical trial. Some participants refused to come to in-person assessments. The online testing had to be prepared for a relatively small group. Changing personal assessments to online ones might be an innovative approach to testing if a positive signal will be proven even in our small subgroups.

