Our clinical trial has several strengths and limitations. First, we prepared a long list of inclusion and exclusion criteria to select appropriate candidates without present or previous brain, neurological, psychiatric, or gastrointestinal diseases and additionally fulfilling other conditions (participation at regular intervals for 6 months, appropriate veins, self-collection of stool and urine, etc.). Second, we created time-efficient recruitment using the electronic questionnaire for data collection from interested volunteers. Third, their memory was evaluated using an electronic test to invite only those with the worst results. This effective type of preselection saves resources and ensures a relatively homogenous group. Fourth, another strength is the comprehensive evaluation of probiotics with many cognitive tests, questionnaires, visual scales, psychological measures, and biological samples involving unusual materials like stool and urine. Fifth, an advantage is the use of probiotics of human origin. Moreover, we add prebiotics to stimulate bacterial growth.

A limitation includes a highly selected study population due to a high number of eligible criteria. The reason was to reduce confounding factors during the trial. Thus, our conclusions cannot be generalized to patients with mild cognitive impairment or deficits. This group of patients should be the next target of a probiotic intervention, although their comorbidities might change outcomes.

In conclusion, we wonder whether manipulating gut microbiota *via* probiotics will favor health conditions in the elderly. This study aims to contribute to this attractive idea in line with the contemporary high interest in interactions between the brain and microbiota.

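### The contrast appears to be probiotic plus fibre against double placebo, but the aim, hypotheses and closing statement name the probiotic alone

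*Protocol article*

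**What the plan says.** **The tablets.** The Trial design section says of the second visit: "Participants also received either probiotic or placebo tablets and fiber or placebo fiber tablets for the next 3 months". The section on probiotics and placebo gives the regimen: "Participants were offered to take one probiotic/placebo tablet each day along with two fiber/placebo fiber tablets". Tablet content is deferred to Supplementary material 2.

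**The conditions.** Trial design describes two groups and two conditions: "Each group received both placebo and probiotics in tandem for 3 months each, but in reverse order".

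**The intervention as the Discussion describes it.** "We chose an intervention using probiotics and prebiotics". The same paragraph says the study explores physical performance, brain functioning and "blood, urine, and stool changes in response to probiotics with prebiotics". The paragraph on strengths adds: "Moreover, we add prebiotics to stimulate bacterial growth".

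**The claims.** The Abstract gives the aim as the effects of human probiotics and predicts that the probiotic group will do better than the placebo group. The section on anticipated results expects favourable change in cognitive, psychological, biological and "other measures following the 3-month probiotic treatment". The Figure 4 legend attaches the expected improvement to the administration of probiotics. The Discussion opens: "We prepared the first 6-month clinical trial to explore the effect of human probiotics in individuals with possible memory deficits". Its last paragraph asks whether changing the gut microbiota through probiotics will benefit health. The limitations paragraph covers only the highly selected population and what follows from it for generalisation.

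**The concern.** If fibre is active whenever the probiotic is active, and placebo whenever the probiotic is placebo, the two components cannot be told apart. The article's formal statements ask about one of them. A positive result reported in those terms would credit the probiotic with a difference that the fibre may have produced in part or in full.

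This matters for outcomes the article lists. Digestion is rated on a visual analog scale. Constipation, flatulence and bloatedness are collected in a questionnaire that ascribes them to the probiotic. Metabolomic and other markers are placed among the primary outcomes as measures of change due to the probiotic intervention. A fibre added in order to act on gut bacteria could plausibly move any of these.

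**Working it through.** **The plan's own figures.** The article gives no figure for the share due to each component. The only numbers attached to this comparison are the detectable effect sizes in the Power calculation section, at 80% power and two-sided α = 0.05. They were reproduced with the noncentral t distribution. For the paired test, the noncentrality is d√n with n − 1 degrees of freedom. For the two-sample test, it is d√[n₁n₂/(n₁+n₂)] with n₁ + n₂ − 2. Group sizes are not in the text shown, so they were assumed from the totals of 91 participants, 72 of them in person.

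| Test | Assumed n | Computed d | Stated d |
|---|---|---|---|
| Paired, all | 44; 45 | 0.432; 0.427 | 0.43 |
| Paired, in person | 32 | 0.511 | 0.51 |
| Two-sample, all | 45/46 | 0.594 | 0.59 |
| Two-sample, in person | 36/36 to 32/40 | 0.670 to 0.674 | 0.67 |

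All four reproduce. They apply to whatever the active and control conditions contain, so the remaining question is what that is.

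**What the conditions contain.**
1. Both tablet types have a placebo version (Trial design; Probiotics and placebo). Fibre is therefore not a constant background given in both periods.
2. Only two conditions are described, in opposite orders (Trial design). No probiotic-only, fibre-only or factorial condition appears.
3. The Discussion names both components as the intervention and says the prebiotic is there to act on bacterial growth, so the fibre is meant to be active.
4. The reading that fits all three is active = probiotic + fibre and control = placebo + placebo fibre. No single sentence states this pairing.

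**What the contrast estimates.** Let P and F be 1 when the probiotic and the fibre are active, and 0 otherwise. Apart from period and participant terms, the expected outcome is

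μ + β_P·P + β_F·F + β_PF·P·F.

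Only (P, F) = (1, 1) and (0, 0) are observed. Their difference is

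β_P + β_F + β_PF.

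That is one estimable quantity made of three unknowns. The sum is identified, but β_P is not. Adding participants makes the sum more precise and does not separate its parts. Comparing within or between participants does not help either, since both use the same two conditions.

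**Wording set against the contrast.**

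| Place in the article | What it names |
|---|---|
| Abstract, aim | Human probiotics |
| Abstract, expected result | Probiotic group against placebo group |
| Anticipated results; Figure 4 legend | Probiotic treatment or administration |
| Discussion, opening | Human probiotics |
| Discussion, choice of intervention and what is explored | Probiotics with prebiotics |
| Discussion, strengths | Prebiotics added |
| Discussion, closing sentence | Probiotics |

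The rows that set the question and the expected answer name one component. The rows that describe the product name both.

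**The case against.** **The article discloses the combination.** Both tablet types are described, the Discussion names prebiotics, and one sentence words the exploration in combined terms. A reader might infer that every statement of purpose hides the fibre; the text does not support that. One can also take the probiotic group as a short label for the active arm. This stands as a limit on the point, but not as an answer to it: the aim and hypotheses still name one component, and no limitation says the two cannot be separated.

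**The pairing is not stated outright.** Supplementary material 2 and the figures are not shown. This stands, and complete joint switching should be described as the natural reading rather than as a documented fact.

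**A combination against a matched double placebo is a legitimate design.** This stands in full. A reader might infer that the comparison is invalid or that a factorial design was required. Neither follows: the trial can answer whether the combination works, and the article gives a reason for adding the fibre.

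**No conclusion has yet been drawn.** This is a protocol article, and its closing sentence poses a question. That is true, but it is also the reason to settle the wording before results are reported.

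**Two further inferences are tempting and unsupported.** One is that the trial claims to show an effect of human strain origin. The article presents origin as a novelty and an advantage of the product, but no hypothesis compares human with non-human strains. The other is that the probiotic's share lies between 0 and 100% of the observed difference. No figure in the article gives such a range, and it is not a true bound: if the components act in opposite directions, the share falls outside it.

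**Conclusion.** The point holds as an inconsistency between what is compared and what is claimed. On the natural reading, the trial estimates the effect of probiotic plus fibre against double placebo, while the aim, the hypotheses, the Discussion's opening and its closing sentence refer to probiotics alone. The probiotic's own contribution is not identified at any sample size, and no numerical share can be assigned to it.

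The effect is on interpretation only. The detectable effect sizes, the tests and the validity of the comparison for the combined product are unchanged. The conclusion rests on one assumption: that active fibre accompanies the active probiotic and placebo fibre accompanies the placebo. If the tablet supplement showed a different pairing, the point would need to be reconsidered.

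**What to change.** Word the Abstract's aim, the hypotheses (including the Figure 4 legend), the Discussion's opening and the planned conclusion as the combined probiotic-plus-fibre product against double placebo. This matches the combined wording the Discussion already uses when it describes what is explored. State the pairing of the two tablet types once, explicitly, in the section on probiotics and placebo. Add to the limitations paragraph that effects cannot be attributed to the probiotic separately from the fibre.

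The cost is wording only, with no change to arms, treatment, data or analysis. The downside is a narrower claim: a positive result would speak for the combination and not for the probiotic by itself.
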